## Abstract

**Background:**

Homoeostasis of the autonomic nervous system (ANS) contributes to cognitive functional integrity in learners and can be greatly influenced by emotions and stress. While moderate stress can enhance learning and memory processes, long-term stress compromises learning performance in a face-to-face classroom environment. Integrative online learning and communication tools were shown to be beneficial for visualization and comprehension but their effects on the ANS are poorly understood. We aim to assess the effects of video conference-supported live lectures compared to on-site classroom teaching on autonomic functions and their association with learning performance.

**Methods and Design:**

Fifty mentally and physically healthy medical students will be enrolled in a randomized two-period crossover study. Subjects will attend a seminar, which is held in face-to-face and simultaneously transmitted *via* videoconference. Subjects will be allocated in two arms in a randomized sequence determining the order in which both seminar settings will be attended. At baseline and throughout the interactive seminar subjects will undergo detailed autonomic testing comprising neurocardiac (heart rate variability), sudomotor (sympathetic skin response), neurovascular (laser Doppler flowmetry) and pupillomotor (pupillography) function. Furthermore, learning progress will be evaluated using pre- and post-tests on the seminar subject and emotions will be assessed using profile of mood state (POMS) questionnaire.

**Statistical Analysis:**

Carryover effects will be handled using a two-way repeated measures (mixed model). Between-group differences (baseline vs face-to-face vs videoconference) will be determined using one-way analysis of variance ANOVA followed by Student–Newman–Keul test.

**Limitations and Strengths:**

This study may elucidate complex interactions between autonomic and emotional dynamics during conventional on-site and video conference-based teaching, thus providing a basis for customized learning and teaching methods. Understanding and utilizing advanced distance learning strategies is particularly important during the current pandemic, which has been limiting on-site teaching dramatically in nearly all countries of the world.

## Introduction

Over the last few decades, multiple digital learning strategies have been designed and are now an essential component of modern curricula. Even before the COVID-19 pandemic has restricted on-site education to a dramatic extent, a growing number of educational institutions offered interactive online lectures and multimodal distance learning programmes. After the outbreak of the pandemic, e-learning, video-conferencing and integrative online learning strategies replaced conventional classroom education entirely in multiple programmes across all disciplines around the globe [1,2]. However, effectiveness of these digital learning techniques as well as their impact on psychophysiology is poorly understood and previous research has shown heterogeneous and partially conflicting results.

This study focuses on the physiological reactions that occur during learning. These reactions are largely mediated by the autonomic nervous system and are closely related to emotions. The theoretical principles for emotional processes in learning is commonly summarized by the Control-Value theory of the achievement emotions, which forms a basis for primarily psychological studies [3]. While both autonomic and emotional changes are relevant to the complex mechanisms of learning and need to be viewed in conjunction with each other, autonomic function assessment allows quantitative evaluation of physiological responses.

In addition, the effects of teaching through the screen in real time are possibly subject to filter effects, such as restricted opportunities for subtle communication and a limited sense of community and competition [4]. These limited degrees of freedom in psychosocial interaction might negatively affect emotions during teaching sessions and thereby alter learning success [5]. Emotions in a traditional classroom are considered to be a dominating factor influencing learning success and are modulated by the classroom atmosphere and surrounding, including social relationship between instructor and classmate as well as learning content and learning methods. While positive emotions in a classroom such as enjoyment, excitement, hope and pride may trigger student’s attention and motivation facilitating the learning process, negative emotions such as anxiety, anger, boredom and shame have an opposite effect and can compromise learning progress substantially [6,7].

Whereas research has shown that mild stress may enhance learning, severe and chronic distress negatively affects learning performance and memory recall [8]. Emotional imbalance and transition from mild positive sympathetic activation to long-term stress can be triggered by subtle and complex aspects in the learning environment. Therefore, understanding the individual effects of different learning forms on emotional and autonomic psychophysiological systems might be crucial in designing effective learning strategies, especially in times of the COVID-19 pandemic, which itself has a profound impact on physical and mental health.

Research suggested that web-based interactive learning may improve students' attention, understanding and visualisation [8]. Conversely, recent studies reported that virtual classroom or distance learning during the pandemic increase anxiety and stress levels by isolation, potentially culminating in depression and serious mental disturbances [9,10]. Relaxation, engagement or stress-affected autonomic functions differently during e-learning [11]. Evaluation of functions of the autonomic nervous system were utilized previously to explore the relationship of learning and emotions. In particular, assessment of autonomic sudomotor function *via* sympathetic skin response (SSR) was used to correlate sympathetic activity with the emotional arousal of students working on online courses [12]. In contrast to interactive student–teacher communication, passive learning in self-study does not seem to affect the autonomic nervous system [13]. Furthermore, visually interactive laboratory work was associated with elevated systolic blood pressure and showed tendencies to altered autonomic neurocardiac and sudomotor function when compared to a face-to-face lecture [14].

Taken together, the complex interaction between emotions, attention and autonomic functions in the context of digital learning strategies as well as traditional classroom-based approaches are poorly understood. Closing this research gap might help facilitate the designing of effective and psychophysiologically healthy learning strategies in times of a global digital transformation of education that has been accelerated substantially by the COVID-19 pandemic.

We aim to characterize the effects of traditional on-site versus videoconference-based education on the autonomic nervous system in medical students and to determine whether changes in autonomic functions during the two seminar forms translate into differences in learning success and stress levels.

## Subjects and methods

### Study subjects

We will include physically and mentally healthy medical students in the first three years of their six-year medical degree programme. Study subjects with a history of cardiovascular or neurological diseases as well as those that are currently under any medical treatment will be excluded from the study. Furthermore, subjects with addiction to drugs or alcohol, smokers and pregnant subjects will be excluded.

### Recruitment

This research project will be advertised to recruit medical students from both medical campuses of Technical University of Dresden: Medical Faculty Carl Gustav Carus in Dresden Germany and Medical Campus Chemnitz at Klinikum Chemnitz gGmbH in Chemnitz, Germany. Student representatives and lecturers will be informed about the rational and study plan of the project. Students who are interested in participating will be contacted by the team of researchers.

### Informed consent

Eligible subjects will be informed in detail about the study protocol. Oral and written informed consent will be obtained from each subject. Subjects will be further instructed to have sufficient night sleep, while caffeine and nicotine consumptions are not permitted within three days prior to measurements.

### Study protocol

Subjects will complete a questionnaire that contains six standard demographic questions and ten questions regarding their medical history. Each subject will be randomized to participate in two learning methods of a preclinical seminar within the same topic, in the order of face-to-face and then videoconference or vice versa under open-label conditions. For the study measurements, there will be two subjects and two investigators in every seminar. One investigator will monitor one study participant for the whole period of the measurement. One participant will start with the traditional face-to-face learning, while the other participant will start with video conference method. Regarding the randomization, we will be using tossing a coin method as a simple randomization. The coin will be tossed by the researcher and the participant will guess the result as “head” or “tail”. Heterogeneity of population will be subsided since we use each participant as its own control by applying a randomized crossover sequence of experimental seminar phases. During the learning session, the subjects will interact only with the instructor. The investigators will interact with the subjects only to attach the electrodes and transducer and give signal when to change learning settings. Throughout the learning sessions, the participant will interact with the same instructor within the same learning topic. Repeating students will not be enrolled in this study. The student who already joined the study measurement will not be included for another measurement.

All measurements will be performed in a temperature and humidity-controlled environment. Measurement time per subject will last around 100 min. This includes measurement at baseline, during seminar settings, and a 10-minute break between settings. The measurements will take place at the same time of day. The study flow is depicted in Figure 1.

**Figure 1. F0001:**
[figure not shown]
Study Flow. Each subject will be randomized into two types of seminars within the same topic. The autonomic function measurements, topic knowledge, and emotions will be assessed at baseline. Each seminar session lasts 40 minutes. Autonomic functions (sympathetic, parasympathetic nervous system) will be assessed and measured at baseline as well as throughout both types of seminars using heart rate variability (HRV), sympathetic skin response (SSR), laser Doppler flow (LDF), and pupillometry. Emotions and knowledge’s related topic test will be given out as Profile of Mood States (POMS) as well as pre- and post-test.

All subjects will be evaluated for autonomic neurocardiac, sudomotor, neurovascular and pupillomotor function as well as emotions and learning progress. Before start of a seminar and baseline measurements, a pre-test covering the content of the seminar as well as the Profile of Mood States (POMS) evaluation will be performed to assess knowledge and emotions [15]. The POMS questionnaire is a valid and widely used tool in clinical psychology to determine emotional status by measuring different dimensions of mood swings over a period of time. Subsequently, autonomic baseline measurements will be performed in which the subject will be laying comfortably in a chair with an open angel of 135 degrees. To assess neurocardiac autonomic function, a three-channel electrocardiogram (ECG) will be attached to the chest recording heart rate variability (HRV) as previously described and detailed in chapter “Neurocardiac autonomic function assessment: heart rate variability” [16]. An sympathetic skin response (SSR) electrode will be placed on the index and middle finger to assess sudomotor autonomic function, whereas an Laser Doppler Flowmetry (LDF) electrode will be placed on the ring finger to assess neurovascular function. as previously described and detailed in chapters “Sudomotor autonomic function assessment: sympathetic skin response (SSR)” and “Laser Doppler Flowmetry (LDF)” [17,18]. All electrodes will be attached to the non-dominant hand. Mobile pupillometry will be used to assess changes of pupil size and velocity. The baseline measurements of autonomic functions will last 240 s and will be undertaken after resting for 180 s prior to the start of the seminar. During each seminar session, HRV, SSR, LDF and pupillometry will be simultaneously recorded. After each interaction with the instructor, the subject will perform three deep inspirations. These breathing patterns allow separate assessment of immediate sympathetic response stimulated by deep inspiration as well as parasympathetic stimulation following metronomic breathing. All amplified and artefact-cleaned neurocardiac, sudomotor and neurovascular and signals as well as breath excursions will be converted to digital data using four-channel digitization hardware (Power-Lab 4/26®, ADInstruments, Castle Hill, Australia). The raw data will be displayed using an analysis software (LabChart Pro® 5, ADInstruments, Castle Hill, Australia). During the 10-min break between two sessions, the subject will be instructed to maintain a resting state avoiding any interaction with other classmates and the instructor. After the end of each seminar session, the subject will complete a post-test and another POMS questionnaire. Details on each assessment technique are given in the following.

### Neurocardiac autonomic function assessment: Heart rate variability

Analysis of HRV will be undertaken to assess neurocardiac function as previously described [16]. Briefly, the monitoring of the heart's actions will be performed *via* a three-channel ECG (MLA2503, ADInstruments, Castle Hill, Australia). For this purpose, three self-adhesive ECG electrodes will be fixed to the upper outer left and right pectoral regions as well as the left lower leg close to the ankle. The analogue signals will be pre-amplified with a digital signal amplifier and artefact filter (Bio Amp® ML132, ADInstruments, Castle Hill, Australia) and digitized with the analogue-to-digital converter (PowerLab®, ADInstruments, Castle Hill, Australia). The generated ECG curve will then be displayed using the analysis software (Chart® 5, ADInstruments, Castle Hill, Australia). The baseline HRV measurement will be performed under resting conditions. The subject will be asked to breath with a usual pace and will be resting for at least 3 min prior to the first section of the seminar. During the seminar, HRV will be continuously monitored. The finger electrode will be placed on the index finger of a subject’s non-dominant hand. The HRV will be assessed *via* Standard Deviation of all NN intervals [intervals between normal R-peaks] (SDNN), Root Mean Square of Successive Differences (RMSSD) and Coefficient of Variation of NN Intervals (CVNN). In addition, spectral analysis will be carried out to quantify very low frequency (VLF), low frequency (LF), high frequency (HF), and the sum of all spectra (TP, total power). HRV analysis will be performed separately for phases of student–teacher interaction, post-interaction deep breathing and interim phases of passive seminar attendance.

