### Statistical analysis plan

The primary endpoint constitutes a group difference in Standard Deviation of all NN intervals (SDNN). Further endpoints encompass a change of remainder functional parameters of the ANS. The study is conceptualized as a pilot study due to lack of preliminary work. Because of the exploratory nature of this study and absent preliminary research using the same assessment techniques we did not undertake a formal sample size calculation. We intend to allocate 48 subjects (*n* = 48) as targeted sample size.

All statistical calculations will be performed using GraphPad Inplot, ISI software and PRISM Version 5.01 (Graphpad Holdings, LLC, CA, USA). Normality will be assessed by descriptive and analytic methods (Shapiro–Wilk test). Under crossover conditions randomization with a two-period, two-treatment design (2 × 2 design) will be performed. In addition, carryover effects between treatments and periods will be tested using two-way repeated measures ANOVA (mixed model). A two-sided *p* > .05 indicates no carryover effects due to sequencing order. Measured values at each treatment period will then be normalized by mean measured values at baseline. Data include HRV parameters (RMSSD, SDNN, VLF, HF, LF, LF/HF, total power), sudomotor parameters (SCL, SSR), neurovascular function parameters (Δt50%down, Δt50%up, VCR), and pupil dynamics (resting pupil diameter, pupil light reflex amplitude and latency, recovery time, NPi). Between-group differences (baseline vs face-to-face vs videoconference) will be determined using one-way analysis of variance ANOVA followed by Student–Newman–Keul test. Not normally distributed data will be analysed either after log-transformation or *via* non-parametric Friedman two-way ANOVA approach. The significance level is set to alpha = 0.05 and two-sided *p* < .05 is considered significant.

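### VLF and total power cannot be validly estimated from the three-breath deep-breathing phase, and baseline VLF from 240 s is imprecise

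*Protocol article*

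**What the plan says.** All references are to the protocol article.

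- **Measures.** The section on neurocardiac assessment plans time-domain measures and says that "spectral analysis will be carried out to quantify very low frequency (VLF), low frequency (LF), high frequency (HF"), together with total power as the sum of all bands.
- **Phases.** The same section continues: "HRV analysis will be performed separately for phases of student–teacher interaction, post-interaction deep breathing and interim phases of passive seminar attendance". It does not limit any measure to particular phases.
- **Length of the deep-breathing phase.** Under Study protocol, in the text after Figure 1: "After each interaction with the instructor, the subject will perform three deep inspirations". No duration or rate is given. That text links the manoeuvre to "parasympathetic stimulation following metronomic breathing", while the sudomotor section calls the inspirations sudden.
- **Baseline.** "The baseline measurements of autonomic functions will last 240 s", after 180 s of rest. The neurocardiac section asks for breathing at the usual pace.
- **Analysis.** The Statistical analysis plan section lists "HRV parameters (RMSSD, SDNN, VLF, HF, LF, LF/HF, total power" among the data. It normalises the values of each treatment period by the baseline mean and compares baseline, face-to-face and videoconference. SDNN is the primary endpoint and the other autonomic measures are further endpoints.

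**The concern.** A record of length T seconds cannot resolve rhythms slower than about 1/T Hz. VLF consists of rhythms with periods from about 25 s to about 5 min, so a block of three breaths is too short to contain most of them. Total power, defined here as the sum over all bands, inherits the gap. Taken literally, the phase-wise plan would produce VLF and total power for the deep-breathing phase that mainly reflect how short the block is. Set beside a longer recording, such values would show a fall in variability that did not occur.

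A milder form of the same problem affects the 240 s baseline, which serves both as divisor and as a comparison condition for sessions of 40 min. The article presents this pilot as a basis for larger studies, so artefactual spectral results could be carried forward.

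**Working it through.** The article gives no figure on this point, so there is nothing to reproduce.

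**Inputs from the article:** three inspirations per block; baseline 240 s; session 40 min = 2400 s; total power is the sum of all bands.

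**Assumptions:** VLF 0.0033-0.04 Hz, LF 0.04-0.15 Hz, HF 0.15-0.40 Hz; 3 to 20 s per breath.

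**Step 1: resolution of the block.** Block length T = 3 × seconds per breath; spacing and lowest resolved frequency = 1/T; breathing frequency = 1/(seconds per breath).

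| s per breath | T (s) | 1/T (Hz) | VLF points | LF points | Breathing peak (Hz) |
|---|---|---|---|---|---|
| 3 | 9 | 0.111 | 0 | 1 | 0.333 (HF) |
| 6 | 18 | 0.056 | 0 | 2 | 0.167 (HF) |
| 8 | 24 | 0.042 | 0 | 3 | 0.125 (LF) |
| 10 | 30 | 0.033 | 1 | 3 | 0.100 (LF) |
| 20 | 60 | 0.017 | 2 | 6 | 0.050 (LF) |

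Widening VLF to 0.003-0.05 Hz still gives 0 to 2 points. Averaging repeated blocks reduces variance but does not lower 1/T.

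**Step 2: LF/HF in the block.** The breathing peak falls below 0.15 Hz when a breath takes longer than 1/0.15 = 6.7 s, that is, fewer than 9 breaths per minute. With faster breaths the block is shorter than 3 × 6.7 = 20 s and LF has at most two points. With slower breaths the respiratory peak may be counted as LF. The ratio is unreliable either way.

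**Step 3: size of the loss.** RR series were simulated with an unchanged spectrum (1500 replicates; low-frequency part 1/f or 1/f^1.5, plus LF and HF peaks; linear detrending, Hann window). Ranges cover the two spectra.

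| Window | VLF, mean/true | VLF CV | Total power, mean/true | Total power CV |
|---|---|---|---|---|
| 30 s | 0.12-0.24 | 1.02-1.03 | 0.48-0.68 | 0.50 |
| 60 s | 0.29-0.45 | 0.90-0.91 | 0.60-0.79 | 0.37-0.38 |
| 240 s | 0.95 | 0.52-0.61 | 0.98-0.99 | 0.23-0.35 |
| 2400 s | 1.03-1.05 | 0.19-0.24 | 1.01-1.03 | 0.08-0.14 |

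A separate simulation (400 series, different spectrum, plain periodogram) agrees. At 30 s, mean VLF was 152 against a true 1000 (15%), and total power was 1703 against 2598 from 40 min (66%). At 240 s, mean VLF was 915 (CV 0.48).

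**Step 4: baseline.** A 240 s record has spacing 1/240 = 0.0042 Hz, 9 VLF points, and 240 × 0.0033 = 0.79 of one cycle at the lower VLF limit. Its mean is nearly right, so the main fault is imprecision. LF and HF are usable (CV 0.26-0.29). Lengthening to 300 s barely helps VLF (CV 0.50-0.61). If a whole 2400 s session is divided by a 240 s baseline, unequal length alone shifts mean VLF by 1.03/0.95 = 1.08 to 1.05/0.95 = 1.11. If a 30 s block were divided by it, the ratio of means would be 0.12/0.95 = 0.13 to 0.24/0.95 = 0.25 with no change in state.

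**The case against.** The strongest reply has four parts.

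- **The article is condensed.** It cites earlier work for HRV methods, so band limits and segment rules may stand in a fuller document. This holds, and their absence is not the point here. The point is that the text expressly includes the deep-breathing phase and exempts no measure. No choice of band limits or pooling gives VLF from three breaths.
- **No phase-wise test is named.** The Statistical analysis plan section speaks of treatment periods, and a treatment period is a 40-min session, from which VLF is well recovered. This also stands. It would be wrong to say that the protocol commits to testing VLF between settings within the deep-breathing phase. It commits to analysing HRV in that phase, and not to how the values are tested.
- **Both settings use the same manoeuvre.** A contrast of face-to-face with videoconference within one phase loses power alike on both sides unless block length or breathing pace differs. This stands too. Equal lengths would remove much of the bias from such a contrast, though a three-breath VLF would remain an extremely noisy estimate of something other than VLF. Comparisons with baseline or between phases are the more exposed ones.
- **Slow breathing is not established.** A reader might infer that deep breathing moves respiratory power from HF to LF and will be misread as an autonomic shift, with LF/HF rising from about 1 to above 100. The article does not support this. It gives no rate and never calls the breathing slow, and that figure requires 240 s of breathing at 0.10 Hz, which the protocol does not contain. The shift is possible only above about 6.7 s per breath.

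**Conclusion.** The point holds in a limited form. VLF, and total power that includes it, are not valid outcomes for the three-breath phase at any assumed pace from 3 to 20 s per breath. LF/HF there is unreliable. These conclusions rest on the usual band limits; the percentages for a 30 s block also depend on the simulated spectra.

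The 240 s baseline is a lesser problem. It would go too far to say that baseline VLF carries no information: about 92-95% of true VLF is recovered on average. It is imprecise, with a CV of about 0.5-0.6 against about 0.2 for 40 min. If normalisation is done subject by subject, that noise enters every VLF ratio.

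Only further endpoints of an exploratory pilot are affected, because SDNN is primary. The change should be made, but no primary conclusion turns on it. Whether SDNN itself is compared over equal windows is a separate question.

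**What to change.** Amend the neurocardiac section and the Statistical analysis plan section as follows.

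1. Exclude the post-interaction three-breath blocks from all spectral parameters. Report that phase with a time-domain breath response, for example the mean over the breaths of maximum minus minimum RR interval.
2. Compute VLF and total power only from segments of equal, pre-stated minimum length in baseline and sessions. Treat baseline-normalised VLF as descriptive, and report whole-session VLF descriptively.
3. Keep LF and HF for interaction and passive segments that meet the minimum length, and report the recorded breathing frequency beside them. Restricting LF and HF to passive segments is not warranted: it would drop the planned interaction phase, and nothing above argues against LF or HF there.

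The cost is wording only. ECG is recorded continuously and breath excursions are already digitised, so no new data are needed. The price is fewer spectral outcomes, and segments below the minimum are not used for spectra. The article does not say how long interactions last, so the minimum should be set with their expected length in mind.
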